### Statistical analysis

The results of this study will provide a preliminary report regarding the efficacy and safety of MA treatment combined with NSAIDs for CNP. All statistical analyses will be performed using IBM SPSS version 19.0 for Windows (Release 19.0 K; IBM SPS Inc., Armonk, NY, USA) and will be based on the Statistics Guidelines for Clinical Trials [22]. The significance level of the tests will be set at 0.05. One-way analysis of variance (ANOVA) and descriptive analysis will be performed to compare baseline characteristics between groups. Trends over time and time-by-treatment interactions will be explored using repeated measures ANOVA. The Chi-square test or Fisher’s exact test will be performed to compare differences in ratios caused by AEs between groups.

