## Background

Chronic neck pain (CNP) is a common musculoskeletal disease with a lifetime prevalence of up to 67% [1]. According to a previous study, the one-year prevalence of neck pain was 29% and 40% for men and women, respectively [2]. In Korea, the lifetime prevalence of CNP is 20.8% [3]. With an increase in dependence on computer and smart phone technology, the prevalence rate of CNP will continue to rise. Pain can be directly related to substantial medicine consumption, absenteeism from work, unemployment, and disability [4, 5]. Therefore, symptom relief is important to improve the quality of life.

Medication, massage, exercise, physiotherapy, and patient education are common methods for the management of CNP [6]. However, the effects of these conventional therapies are limited and the validity of many CNP treatment guidelines is unclear [6, 7]. Although pain-control drugs such as non-steroidal anti-inflammatory drugs (NSAIDs) are one of the most commonly used drugs for CNP, their long-term use carries a risk of side effects and intolerance [8]. Modalities from the field of complementary and alternative medicine (CAM) are also frequently used for treatment [9]. These include acupuncture, herbal medicine, cupping, moxibustion, and pharmacopuncture [10]. Patients with chronic musculoskeletal disease tend to utilize both conventional and CAM treatments for more positive outcomes [11].

Miniscalpel acupuncture (MA) tends to exert better therapeutic effects on chronic musculoskeletal pain compared with regular acupuncture treatment [12]. MA combines Traditional Chinese Medicine meridian theory and modern surgical principles and it requires an understanding of anatomical structures. The aim of MA is recovery of the kinetic state of soft tissue through peeling adhesion and removal of attached tissues [13], with the advantage of quicker recovery and pain reduction compared with regular acupuncture [14]. Furthermore, it shows superior and long-lasting effects compared with regular acupuncture [15].

Although CAM and conventional treatment modalities are frequently applied in combination, their efficacy and safety have rarely been investigated in clinical trials. In this pilot study, we will investigate the efficacy and safety of MA combined with NSAIDs in patients with CNP. The results will provide clinical evidence for evaluating the feasibility of large-scale randomized controlled trials (RCTs) of this combination treatment for CNP.

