## Methods/Design

### Design

The protocol of this assessor-blinded RCT follows the Declaration of Helsinki and Korean Good Clinical Practice. The study will be conducted at Daegu Oriental Hospital of Daegu Haany University, Daegu, Republic of Korea. Independent researchers blinded to randomization will assess the outcomes and analyze statistics. Informed consent to participate in the clinical trial will be obtained after the researcher provides sufficient information and explanations regarding the study interventions. This protocol follows the SPIRIT guidelines and the checklist and figure are available at the end of the manuscript.

This study is designed as a pilot trial to calculate the appropriate sample size for further RCTs. Each group will include 12 participants, allowing for a 20% dropout rate for evaluating the pragmatic purpose of this trial. A total number of 36 participants will be included, which is larger than the minimum number recommended for pilot studies (Additional files 1 and 2).

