### Outcomes

The primary outcome will be measured using VAS. Changes in VAS scores after three weeks of treatment will be measured relative to the baseline scores and will be considered the primary outcome. The secondary outcome will be determined by the Neck Disability Index (NDI), EuroQol 5-dimension (EQ-5D) questionnaire, and Patient Global Impression of Change (PGIC) scale. Outcomes will be measured at weeks 0 (baseline), 1, 2, 3 (primary end point), and 7 (four weeks after treatment completion). Outcome measurements will be recorded by two independent researchers. Table 1 shows the treatment and outcome measurement schedules.

**Table 1 Tab1:** Treatment and outcome measurement schedules during our pilot study

Outcome measures	Screening	Week 0 (baseline)	Week 1	Week 2	Week 3	Week 7
Screening test	V					
Sociodemographic characteristics	V					
Randomization		V				
Laboratory test	V				V	
MA treatment		V	V	V		
NSAIDs prescription		V	V	V		
Visual analog scale	V	V	V	V	V	V
Neck Disability Index		V	V	V	V	V
EQ-5D questionnaire		V	V	V	V	V
PGIC scale			V	V	V	V
Adverse events		V	V	V	V	V
Credibility assessment					V	
Total safety assessment					V	

*NSAIDs* nonsteroidal anti-inflammatory drugs, *EQ-5D* EuroQol 5-dimension, *PGIC* Patient’s Global Impression of Change

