### Primary outcome measurement

VAS is a 10-cm measurement instrument to determine the severity of pain. A 10-cm horizontal line will be used. The individuals rate his or her pain on a scale of 0–10, where 0 indicates the absence of pain and 10 indicates the worst pain imaginable. Participants will estimate their level of pain by marking on the line. Then the distance from “absence of pain” point will be measured [17, 18]. In this study, the VAS score will indicate pain at the point of measurement. Changes in VAS scores after three weeks of treatment, relative to the baseline scores, will be considered the primary outcome.

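### The stated efficacy analysis, an omnibus time-by-treatment test, is not aligned with the week-3 VAS endpoint or with the combined-versus-single-treatment question

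*Protocol article*

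**What the plan says.** The section on primary outcome measurement states: "Changes in VAS scores after three weeks of treatment, relative to the baseline scores, will be considered the primary outcome". The Outcomes section says the same and marks week 3 as the primary end point among visits at weeks 0, 1, 2, 3 and 7. The Background gives the question: "we will investigate the efficacy and safety of MA combined with NSAIDs in patients with CNP". The arms are MA, NSAIDs and the two combined.

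The Statistical analysis section gives each method a purpose:
- Baseline: "One-way analysis of variance (ANOVA) and descriptive analysis will be performed to compare baseline characteristics between groups".
- Efficacy: "Trends over time and time-by-treatment interactions will be explored using repeated measures ANOVA".
- Adverse events: chi-square or Fisher's exact test.
- Level: "The significance level of the tests will be set at 0.05".

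The Design and Participants sections say that the pilot is meant to supply the sample size for a full-scale trial. The Discussion adds that it should help in calculating the effect size.

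**The concern.** Each named method has a target, and none of the targets is the week-3 difference in VAS between arms. The one efficacy method asks whether the arms' profiles over all visits are parallel. That question has no preferred time point and no preferred pair of arms, whereas the endpoint has one time point and the study question has two pairs: combined versus NSAIDs and combined versus MA.

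A significant interaction would therefore not show that the combination adds anything at week 3, and a non-significant one would not rule it out. For a pilot, the larger loss is in planning. The next trial needs a week-3 difference, its residual SD and an interval around the difference, and an interaction F test is none of these. The article also names no baseline covariate, which costs precision when arms are this small.

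**Working it through.** **Inputs from the article.** Three arms, five visits, 12 per arm, level 0.05 (two-sided assumed). The total reproduces: 3 × 12 = 36. The Design section says: "Each group will include 12 participants, allowing for a 20% dropout rate". That leaves 12 × 0.8 = 9.6 evaluable per arm. No SD, correlation, effect size or power is stated, so those used below are assumptions.

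**1. What the test covers.** With week 0 as a level of time, the interaction has (3 − 1)(5 − 1) = 8 numerator and (36 − 3)(5 − 1) = 132 error degrees of freedom with complete data. The article does not say whether week 0 is included. Without it, the numerator is (3 − 1)(4 − 1) = 6.

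**2. What makes it significant.** The simulations used 12 per arm and equal correlation r between visits. In the first two scenarios the benefit was about 0.33, 0.67, 1.0 and 0.5 SD at weeks 1, 2, 3 and 7. Entries are the share of trials with a significant interaction.

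| Scenario | r = 0.3 | r = 0.5 | r = 0.7 |
|---|---|---|---|
| Combined better than both, uncorrected F | 36% | 49% | 78% |
| Combined equal to MA, both better than NSAIDs, uncorrected F | 35% | 51% | 76% |
| Combined better than both, Greenhouse-Geisser | 33% | 46% | 72% |
| Combined equal to MA, both better than NSAIDs, Greenhouse-Geisser | 31% | 44% | 73% |
| Combined differs from both only at week 7, by 1 SD, Greenhouse-Geisser | 49% | 66% | 91% |

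The uncorrected range for the week-7-only scenario was 52–91%. The test does not separate the first scenario from the second. In the second and in the week-7-only scenario, the week-3 contrast of combined versus MA was significant in about 4–6% of trials, as it should be.

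**3. What baseline adjustment is worth.** With unit SD at both visits and baseline-to-week-3 correlation r:
- change-score variance = 2(1 − r)
- baseline-adjusted variance = 1 − r²
- ratio = (1 − r²) / [2(1 − r)] = (1 + r)/2

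The ratio is 0.65, 0.75 and 0.85 at r = 0.3, 0.5 and 0.7. As an example, take SD 2 cm, r = 0.5 and 12 per arm. The standard error of a pairwise difference is 2 × √1.00 × √(2/12) = 0.82 cm for change and 2 × √0.75 × √(2/12) = 0.71 cm adjusted.

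**4. What the next trial needs.** The pairwise 95% half-width is t × SD × √(2/n), where SD is that of the analysed quantity. With 12 per arm (33 degrees of freedom) it is 1.25, 1.66 and 2.08 cm for SD 1.5, 2.0 and 2.5. With 10 per arm it is 1.38, 1.84 and 2.29 cm. The interaction test reports no such interval.

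**5. Illustrative power.** At r = 0.5, 12 per arm and a 1 SD week-3 benefit over both arms, both adjusted contrasts were significant in about 64% of trials, against 49% for the uncorrected interaction. A single adjusted contrast gave 77%, but that answers only half the question.

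**The case against.** The strongest reply is that the article is a condensed account of a pilot. It promises a preliminary report, claims no power, calls the repeated-measures analysis exploratory and refers to a statistics guideline that is not shown. Contrasts and covariates may be in a full protocol or analysis plan. Week-3 means and SDs could also be summarised from the collected scores. Much of this stands. The article does not prove that a week-3 comparison is absent from the trial's analysis, only that the analysis it chose to state does not match the endpoint it states.

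A reader might infer more in four places, and the text does not support it:
- **Baseline is ignored.** If week 0 is a level of time, the interaction compares changes from baseline, which agrees with the primary outcome as defined. What is lost is the efficiency of covariate adjustment. Both approaches are valid under randomisation.
- **A steady benefit on the Patient Global Impression of Change would be missed.** The article does not say that this scale will be analysed by repeated-measures ANOVA.
- **Type I error is inflated by non-sphericity.** The article does not say that the uncorrected F will be used.
- **Family-wise error is inflated by pairwise testing.** The article proposes no set of pairwise tests.

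It is also fair to say that a contrast aimed at the assumed effect will tend to beat an omnibus test by construction. The power comparison is therefore not the main argument.

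**Conclusion.** The point holds as a mismatch inside the article. The endpoint is at week 3 and the question concerns two contrasts, but the stated method is an omnibus interaction over all visits and arms. The test's 8 degrees of freedom (if week 0 is included) and the variance ratio (1 + r)/2 are arithmetic, though the range 0.65–0.85 assumes r between 0.3 and 0.7. The simulated percentages rest on assumed effects, SD and correlation and are illustrative only.

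A reader might go further and call for a formal rule that superiority requires both contrasts to be significant, or treat the power gap as a defect that must be repaired. Neither suits a pilot with no power claim. The consequence that matters is that the stated analysis does not itself deliver the week-3 difference, residual SD and interval that the pilot exists to provide.

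**What to change.** In the Statistical analysis section, state as the primary analysis a linear model of week-3 VAS (or change to week 3) on treatment arm, with baseline VAS as covariate. Report combined versus NSAIDs and combined versus MA, each with a 95% confidence interval, together with the residual SD. Treat NDI and EQ-5D in the same way, since both are measured at week 0. Keep repeated-measures ANOVA for exploratory trends, and say whether week 0 is a level of time.

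The cost is a few sentences, ideally settled before the data are analysed. Table 1 already schedules VAS at baseline and week 3, and the named software fits the model. No visit, measurement or patient is added.

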### Randomization and allocation concealment

The 36 patients will be randomized using simple randomized procedures, with a 1:1:1 allocation ratio. Written informed consent will be obtained before randomization. Random numbers will be generated by an independent statistics professional using SPSS version 19.0 for Windows (release 19.0 K; SPSS Inc. Armonk, NY, USA). Sealed opaque assignment envelopes will be used for allocation concealment. The participants will be allocated into the predefined treatment arms. Allocation concealment will not be broken until study completion. The treatment arm and random number of an individual participant will be recorded in the case report form and randomization table. Outcome assessors and data analysts will be blinded to interventions.

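### Unless missing values are imputed, the named repeated measures ANOVA discards observed week-3 pain scores from any patient who misses another modelled visit; a mixed model would keep them.

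*Protocol article*

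**What the plan says.** The Statistical analysis section of the protocol article gives one method for outcomes followed over time, covering trends as well as interactions: "time-by-treatment interactions will be explored using repeated measures ANOVA". One-way ANOVA is reserved for baseline characteristics, and chi-square or Fisher's exact tests for adverse events. On software it says "All statistical analyses will be performed using IBM SPSS version 19.0 for Windows".

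The Outcomes section sets five time points: "Outcomes will be measured at weeks 0 (baseline), 1, 2, 3 (primary end point), and 7 (four weeks after treatment completion". The primary outcome is the change in VAS from baseline to week 3.

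On numbers, the Design section states "Each group will include 12 participants, allowing for a 20% dropout rate for evaluating the pragmatic purpose of this trial". The Withdrawal and dropout section lets participants leave at any time.

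The article does not say how missing visits are handled, which visits enter the model, or whether the week-3 change is tested separately.

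**The concern.** Classical repeated measures ANOVA, as run in the SPSS general linear model procedure, treats each patient's visits as one complete vector. A single gap among the modelled visits removes the whole patient. Week 7 falls four weeks after treatment ends, so a patient can easily supply the primary measurement at week 3 and still be missing later. That patient's week-3 score would then count for nothing in the only efficacy model that the article names.

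The pilot exists to size a full-scale trial: the Design, Participants and Discussion sections all say so. An effect size and SD taken from completers feed straight into that calculation. If the patients who leave differ in pain from those who stay, and more so in one arm than another, both quantities can be distorted. Patients know whether they receive the procedure, tablets or both, so dropout that differs by arm is plausible, although nothing in the article establishes it.

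**Working it through.** **Inputs from the article.** 36 patients, 12 per arm, three arms; 20% dropout allowance (Design). Visits at weeks 0, 1, 2, 3 and 7 (Outcomes). Repeated measures ANOVA in SPSS 19.0 (Statistical analysis).

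**1. The plan's own figure.** 3 × 12 = 36, as stated. No power, effect size, SD or pre-dropout number is given, so nothing further can be reproduced.

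**2. Complete cases at the planned dropout.** 36 × (1 − 0.20) = 28.8, about 29 in total; 12 × 0.80 = 9.6 per arm.

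**3. Adding sporadic missed visits.** Assume that each of the four post-baseline visits is also missed independently with probability m among those who do not drop out. Complete cases = 28.8 × (1 − m)^4:

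| m (assumed) | complete cases |
|---|---|
| 1% | 27.7 |
| 2% | 26.6 |
| 3% | 25.5 |
| 5% | 23.5 |

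**4. Week-3 values thrown away.** Let s be the share of dropouts who leave only after week 3 (assumed). Patients with a week-3 VAS = 36 × [1 − 0.20 × (1 − s)]. Without imputation, a week 0–7 model still uses only 28.8.

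| s (assumed) | have week-3 VAS | observed week-3 values discarded |
|---|---|---|
| 25% | 30.6 | 1.8 |
| 50% | 32.4 | 3.6 |
| 75% | 34.2 | 5.4 |

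**5. Precision.** Going from 12 to 9.6 per arm widens a between-arm interval by √(12/9.6) = 1.12.

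**6. Illustration of selection bias.** Assume normal scores, that the worst 20% at week 2 in one arm leave before week 3, and a correlation of 0.6 between week 2 and week 3.
- Shift in the retained week-2 mean: −φ(0.842)/0.80 = −0.280/0.80 = −0.35 SD.
- Carried to week 3: 0.6 × (−0.35) = −0.21 SD. A simulation of 400,000 patients gave −0.209 SD for complete cases and 0.0007 SD for a regression using the observed weeks 0 to 2.
- If the SD were 2 cm (assumed), 0.21 × 2 is about 0.4 cm.
- Spread: the retained week-2 variance is 1 − 0.842 × 0.35 − 0.35² = 0.583. The week-3 variance is then 1 − 0.6² × (1 − 0.583) = 0.85, so the week-3 SD is about 0.92 of its true value in that arm.

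**7. The same illustration for change from baseline.** Dropping those patients also shifts the retained baseline mean, by r × (−0.35), where r is the correlation of baseline with week 2. The bias in the change, in SDs of a single score and with equal SDs at each visit, is −0.35 × (0.6 − r):
- r = 0.6: 0
- r = 0.3: −0.105 SD
- r = 0: −0.21 SD

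So 0.21 SD applies to the week-3 mean. For the change score it is the top of the range as r runs from 0.6 down to 0.

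**The case against.** - **Deletion is not certain.** It follows only if nothing is imputed first, and losing patients for a missed week 7 requires week 7 to be in the model. The article says neither, and the full protocol or analysis plan may settle both. This stands: silence on missing data is not itself a fault here, and the point must be stated conditionally.
- **The role of the model is soft.** The article says that trends and interactions are explored; it never says that this model tests the week-3 change. A reader might infer that the primary analysis is a completers analysis, but the text does not support that. What remains is that no other efficacy method is named. Even if week 3 were tested separately, the longitudinal analysis would lose these patients.
- **The 20% is a planning margin.** A reader might take about 29 completers as a shortfall, or the 20% as a forecast. Neither holds: the text is "allowing for a 20% dropout rate", and 12 per arm already includes it.
- **The bias figure comes from a chosen mechanism.** Dropout is confined to one arm and set entirely by recorded week-2 pain, which is the case in which a likelihood model does best. Loss through side effects or unrecorded pain need not be corrected. With an SD of 2 cm, 0.4 cm is also less than half the standard error of a between-arm difference, 2 × √(2/9.6) = 0.91 cm. For the change from baseline the bias may be smaller still, or nil. All of this stands, and the figure is no more than an illustration.
- **For an exploratory pilot this is preference.** In part. But discarding observed values of the primary measurement has no offsetting benefit when the alternative runs in the same software.

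**Conclusion.** The point holds in conditional form. Repeated measures ANOVA is the only post-baseline efficacy method named. Unless values are imputed, it uses only patients with every modelled visit. At the planned allowance that is about 29 of 36 for weeks 0 to 7, and about 23 to 28 if some visits are also missed sporadically at 1% to 5% each (assumed). If a quarter to three quarters of dropouts leave after week 3 (assumed), roughly 2 to 5 observed week-3 scores are discarded.

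The harm is wasted data and possible selection bias in the effect size and SD meant for the full trial, not a missed recruitment target. About 0.2 SD in one arm's week-3 mean illustrates the bias under the stated assumptions; for the change from baseline it lies between 0 and 0.21 SD as the baseline correlation falls from 0.6 to 0. The documents do not show that dropout will be related to pain or will differ by arm, nor that the randomised comparison will fail. This is a change worth making, not a fatal flaw.

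**What to change.** In the Statistical analysis section, replace repeated measures ANOVA with a likelihood-based linear mixed model for repeated measures:
- outcome: VAS at weeks 1, 2, 3 and 7;
- fixed effects: arm, visit, arm-by-visit and baseline VAS;
- patients: all randomised patients with any post-baseline value, in their assigned arm;
- estimates: the week-3 between-arm contrasts with confidence intervals.

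Prespecify the covariance structure, a simpler fallback if the model does not converge, and a small-sample degrees-of-freedom method, since each arm has only 12 patients.

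The cost is a change of wording and slightly more analysis work in SPSS, with no new data. Two limits remain. Patients with no post-baseline value still contribute nothing. The bias is removed only when missingness depends on recorded data, so the reasons for missed visits should be reported by arm.

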### Data monitoring

A qualified clinical research associate will oversee study protocol compliance, informed consent documents, overall progress of the trial, participant recruitment, data quality and timeliness, performance of the interventions, and all fields and process of the trial. If any important protocol modifications or violations exist, an amended protocol will be resubmitted and reported to the relevant parties (e.g. investigators, IRB, trial participants, trial registries, and sponsor).

## Discussion

The current management of CNP involves a comprehensive approach including pharmacological and non-pharmacological interventions. Recently, there have been increased interests in the use of CAM modalities for the treatment of CNP. CAM modalities have recently been receiving more attention for pain control. Acupuncture is the one of the most widely known CAM modalities. In previous studies, acupuncture was proven effective for the treatment of CNP [23]. Of late, a variety of acupuncture treatments such as thread embedding therapy, MA, and pharmacopuncture are being practiced in Korea; these tend to exert better effects compared with traditional acupuncture [24, 25].

The use of MA is increasing in Korea. From January 1999 to May 2014, 28 clinical research papers on MA were documented in Korea [26], and this approach has come to be widely used for the treatment of musculoskeletal diseases [27]. In a review of trends regarding MA in Korea, 87.1% MA studies pertained to musculoskeletal disease and approximately 14.7% of the musculoskeletal diseases involved neck pain. MA is reportedly effective for the management of cervical herniated intervertebral discs and other cervical diseases such as ossification of the posterior longitudinal ligament [28, 29]. As stated above, previous studies have indicated positive results regarding MA treatment for neck pain, although clinical studies on combination treatment involving western medicine approaches such as the use of painkillers and MA are lacking.

The present study will be conducted by researchers trained to follow the study protocol and good clinical practice guidelines. Methodological integrity and scientific validity will be guaranteed with strict supervision and monitoring. The results of this study will contribute to a better understanding of the efficacy and safety of MA treatment alone and in combination with NSAIDs, which are frequently used for the treatment of CNP. Furthermore, they will provide guidelines for the development of a relevant protocol for conducting a RCT of MA treatment combined with NSAIDs for CNP and will aid researchers in calculating the effect size for such full-scale RCTs. Finally, they will provide evidence regarding the combination of Korean and western medicine modalities for the management of CNP.

